## Abstract

**Background:**

Obesity in young children remains a public health concern, and maternal weight is one of the strongest predictors of obesity in early childhood. However, parental adherence in interventions for young children is often low and existing programs have had mixed success. An innovative approach to treatment is needed that increases adherence among mothers and improves weight-related behaviors simultaneously in mothers and children. The objective of the Smart Moms randomized controlled trial (RCT) is to test the efficacy of a 6-month primarily smartphone-delivered program to reduce sugar-sweetened beverage and juice consumption among children ages 3–5 whose mothers are overweight or obese. This paper describes the study design and intervention.

**Methods/Design:**

Mother-child dyads were eligible if the mother was overweight or obese, owned a smartphone, and if the child was between the ages of 3–5 and consumed 12 oz or more per day of sugar-sweetened beverages (SSBs) and 100 % fruit juice. Participants were randomly assigned to the Smart Moms intervention or a waitlist control group. The intervention consisted of theoretically grounded and evidence-based behavioral strategies delivered through one group session, lessons on a mobile-optimized website, and text messages. Mothers submitted self-monitoring information via text message and received regular tailored feedback emails from interventionists. The primary outcome is change in child SSB and juice consumption and a secondary outcome is change in maternal weight.

**Discussion:**

This Smart Moms study was designed to determine if a low-burden intervention delivered using mobile methods and targeted towards mothers could be effective at changing child sugar-sweetened beverage intake. Results will indicate if mobile-based methods can be a feasible way to engage mothers in family-based studies and will inform successful strategies to prevent childhood obesity through parent-targeted approaches.

**Trial registration:**

Clinicaltrials.gov NCT02098902 (Registered March 25, 2014).

## Background

Over the last 40 years, research has confirmed a trend for the onset of obesity at increasingly younger ages. One in three low-income children are overweight by age 5 [1] and the majority of children who become overweight or obese reach overweight status before the age of 5 [2]. This is concerning because excessive weight gain in early childhood is known to increase the risk of obesity and its health-related consequences throughout childhood and into adulthood. To reduce the risk of obesity, it is imperative to focus on increasing children’s healthy weight behaviors and preventing weight gain beginning at an early age.

### Maternal weight and sugar-sweetened beverage consumption as risk factors

While there are many determinants of early childhood obesity, some of the strongest and most consistent predictors are maternal weight and weight-related behaviors [3, 4]. Thus, children of overweight and obese mothers are at particularly high risk for obesity during their childhood years. Before the age of five, children are socialized primarily in the family environment with parents serving as “gatekeepers” in the home by providing specific diet and activity opportunities for children. Intervening with overweight and obese mothers to make the home environment healthier and make dietary changes for themselves and their children could reduce the risk of the child becoming overweight.

The child’s own dietary behaviors, above and beyond those associated with maternal weight and diet, are also predictive of child overweight [5]. Sugar-sweetened beverage (SSB) intake is one of the dietary factors most consistently associated with early childhood obesity across studies [4, 6]. NHANES data indicates that, on average, children in this age range are consuming an average of 70 cal a day from sugary drinks including caloric carbonated beverages, fruit drinks, and sport drinks [7]. This increases to 176 calories a day when including consumption of 100 % fruit juice [8]. Intervention evidence in children ages 4–12 has shown that replacing SSBs with noncaloric beverages can lead to a lower increase in BMI z-scores over 18 months compared to children making no reduction in SSBs [9]. Thus, intervening with mothers to reduce child sugar-sweetened beverage consumption seems to be a promising target for intervention to prevent early childhood obesity.

### Existing parent-targeted interventions

Interventions among school-aged children and among preschool-aged children within childcare centers and preschools have shown that the active involvement of the parent is a critical factor for success [10–12]. But unfortunately, interventions requiring parent involvement often have low adherence and high dropout rates. For example, in a study that targeted mothers and their preschool-aged children that did not result in changes in child diet, physical activity, or sedentary behaviors, participants participated in half of the required phone calls, less than half of the participants attended the group session, and 68 % completed the follow-up assessment at 12 months [13]. While there have been several parent-targeted interventions that have successfully led to changes in young children’s diet or physical activity behaviors, participation in these interventions has also been low and successful behavior change among parent–child dyads was associated with greater treatment adherence [13–16].

Even in studies that have targeted mothers only with no focus on changing the child’s behavior, attendance and retention are typically low, particularly among those that have required face-to-face group meetings [17]. As an example, a study with mothers of children ages 1–4 that involved 8 weekly 2-h classes had only 44 % of participants in attendance at the first session, and attendance continued to decrease over time [18]. In a large RCT of postpartum women with 18 in-person group meetings and additional telephone calls focusing on healthy eating and physical activity, the group meetings had only 27 % attendance. Overall, attendance at group meetings was positively associated with weight loss [19].

### Intervening with mothers of young children to reduce child SSBS and juice

Young children of overweight and obese mothers often engage in behaviors similar to their mothers, including SSB consumption, and thus are at high risk of becoming overweight or obese [20, 21]. Moreover, mothers of young children are more likely to be overweight or obese due to the time demands and life transitions that occur when having children [22, 23]. Targeting mothers who are overweight or obese as the agent of change in the household could be a promising way to improve child dietary behaviors while also helping the mother lose weight. Because mothers face many barriers to weight control behavior change, including time demands and lack of childcare, there is a need for interventions that are uniquely targeted to the needs of mothers and children. A smartphone-based intervention that requires relatively few in-person visits might increase adherence by reducing mothers’ travel time, providing a flexible schedule, and minimizing the amount of time spent participating in study activities.

Interventions using text messages and mobile-based websites have the capability to reach many people, as mobile phone use is high and continues to increase among adults in the United States. Among the 91 % of Americans who own a cell phone, 63 % of them use it to access the internet or email [24]. There has been a widespread adoption of eHealth and mHealth interventions in recent years, many of which have been effective in producing clinically meaningful changes in behaviors and weight loss [25–28]. However, surprisingly few studies have used the internet and/or text messages to reach parents of young children, and there have been no mobile-based studies that have targeted a parent to reduce their child’s SSB/juice intake. A critical next step in the literature is to use innovative treatment approaches that might increase adherence among mothers in order to improve weight-related behaviors in both mothers and children. Thus, the objective of this study is to test the efficacy of a 6-month smartphone-based program that targets mothers who are overweight or obese to reduce the SSB and juice consumption of their preschool-aged children compared to a waitlist control group.

## Methods/Design

### Study design

Smart Moms is a two-group randomized controlled trial designed to test the efficacy of a 6-month program to reduce SSB and juice consumption among children ages 3–5 of mothers who are overweight or obese compared to a waitlist control group. Mother-child dyads were randomly assigned to the Smart Moms intervention group or to a waitlist control group after baseline data were collected. Randomization was stratified by two factors: whether or not the child was in childcare/kindergarten and child baseline SSB/juice intake. The primary hypothesis is that the Smart Moms program will result in a greater reduction in child fluid ounces of SSBs and juice compared to the control group at 6 months. Secondary outcomes include maternal percent weight loss, maternal caloric beverage consumption, and child BMI z-score at 6 months. The study was approved by the UNC non-biomedical IRB on March 18, 2014.

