### Sample size and statistical analysis

The primary outcome for the study was change in child SSB/juice intake in fluid ounces from baseline to 6 months. Based on evidence from three previous studies that resulted in significant SSB/juice reductions in children [14, 29, 30], the study was powered to detect a difference of a 6-oz reduction between groups at 6 months, with a within-group standard deviation of 6.0. Therefore, with 80 % power at an alpha level of .05 and accounting for 20 % attrition, the study required 21 participants per group for a minimum of 42 total participants to detect a significant difference in SSB/juice reduction.

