### Measures

Participants completed assessments at baseline (prior to randomization), 3 months, and 6 months. Each assessment period included an in-person visit and the completion of online questionnaires. Participants in either treatment group who missed assessment visits were contacted frequently by phone and email to schedule and complete assessment visits. Participants received a $20 honorarium for completing each of the 3- and 6-month assessments, meaning participants who completed both assessments received $40 total.

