### Data analysis

SAS version 9.3 (Cary, NC) will be used to conduct statistical analyses for the primary and secondary analyses of this intervention. Intent-to-treat analyses using linear mixed models will be used to examine changes in the primary and secondary outcomes. The linear mixed models will include a random intercept and effects for treatment group, time, and group by time interactions for both follow-up visits. A Bonferroni adjustment will be used to account for the effect of comparisons at multiple time points. Any characteristics found to be associated with both treatment group and the outcomes will be defined as confounders and will be included as covariates in analyses.

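### Randomisation is stratified by childcare status and baseline SSB/juice intake, but the planned model conditions on neither as a covariate, which costs power and can make the test conservative

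*Protocol article*

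**What the plan says.** Protocol article, Study design: "Randomization was stratified by two factors: whether or not the child was in childcare/kindergarten and child baseline SSB/juice intake". The cut-point for intake, the measure used to form the strata and the block size are not given.

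Protocol article, Data analysis: "The linear mixed models will include a random intercept and effects for treatment group, time, and group by time interactions for both follow-up visits". The one stated route for covariates follows: "Any characteristics found to be associated with both treatment group and the outcomes will be defined as confounders and will be included as covariates". On multiplicity: "A Bonferroni adjustment will be used to account for the effect of comparisons at multiple time points".

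Protocol article, Sample size and statistical analysis: "The primary outcome for the study was change in child SSB/juice intake in fluid ounces from baseline to 6 months", and "the study was powered to detect a difference of a 6-oz reduction between groups at 6 months", with a within-group SD of 6.0, 80% power, alpha .05 and 20% attrition, giving 21 per group.

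Protocol article, Measures: "Participants completed assessments at baseline (prior to randomization), 3 months, and 6 months". Baseline is thus one of three repeated measurements of the primary response.

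**The concern.** Stratifying on baseline intake makes the arms more alike at baseline than simple randomisation would. The true sampling variance of the difference in mean change falls accordingly. A model that takes the group-by-time contrast without conditioning on baseline estimates its standard error as if that balance had arisen by chance. The standard error is then too large and the test rejects a true null less often than its nominal level.

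Apart from calibration, change from baseline is a less precise contrast than one conditioned on baseline whenever the baseline-to-follow-up correlation is below 1.

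The covariate rule works against the design. It requires an association with arm, which stratification is meant to prevent, so the factors judged important at randomisation are among the least likely to be adjusted for. At stake is power in a trial planned with a minimum of 42 dyads.

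**Working it through.** **Inputs.** From the protocol article: difference 6 oz, SD 6.0, alpha .05, power 80%, attrition 20%, 21 per group, visits at baseline, 3 and 6 months. Assumptions, because the article does not give them: SD 6.0 is the SD of change; tests are two-sided; baseline-to-follow-up correlation rho is 0.2 to 0.6; intake strata are a median split; permuted blocks of 4; half the children in childcare; Bonferroni over two visits gives 0.025 each.

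**1. The plan's own figure.** Normal approximation: n = 2 × (1.96 + 0.84)² × 6²/6² = 15.7, so 16 per arm. The exact t test needs 17 (power 80.7%). For attrition, 17/0.8 = 21.25 and 17 × 1.2 = 20.4, so the stated 21 is reproduced to rounding. Completers: 42 × 0.8 = 33.6, about 34.

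**2. Analytic check on baseline intake.** Let s be the single-visit SD.
- Variance the change contrast assumes, per child: 2s²(1 − rho) = 36.
- Variance given baseline: s²(1 − rho²) = 36 × (1 + rho)/2.
- With perfect baseline balance, the ratio of true to model variance is therefore (1 + rho)/2.

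At rho 0.2 the ratio is 0.6, the effective critical value is 1.96/√0.6 = 2.53, and the null rate is 1.1%. At rho 0.6 the ratio is 0.8 and the rate is 2.8%. These are bounds, since stratification does not balance baseline perfectly.

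Standard errors with 17 per arm: planned contrast 6 × √(2/17) = 2.06. Conditioned on baseline, multiply by √((1 + rho)/2): 1.59, 1.72 and 1.84 at rho 0.2, 0.4 and 0.6.

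**3. Simulation of the planned three-visit model.** Strata were cut on the recall value, with 34 completers and complete data. The comparison is a 6-month regression on group, baseline intake and childcare.

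| | rho 0.2 | rho 0.4 | rho 0.6 |
|---|---|---|---|
| Null rate at 5%, planned | 2.8% | 3.3% | 3.6% |
| Null rate at 5%, adjusted | 5.2% | 4.9% | 4.7% |
| Power at 5%, planned | 85.2% | 84.1% | 83.6% |
| Power at 5%, adjusted | 95.7% | 91.0% | 88.6% |
| Power at 2.5%, planned | 76.2% | 74.2% | 75.3% |
| Power at 2.5%, adjusted | 91.5% | 85.8% | 80.9% |

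Repeat runs put the planned null rate at 2.4–3.7%. They put power at about 82–85% against 88–95% at 5%, and 73–76% against 80–91% at 2.5%; these are the rounded ranges used here. With 42 analysed, the model standard error is about 1.85 against an empirical 1.64–1.75, so it is 6–13% too large. Without stratification the same model holds 4.7–5.3%, so the conservatism comes from stratifying and then not conditioning.

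**4. Childcare alone** (stratified on childcare only, rho 0.4, 42 analysed). A constant effect of 0.8 single-visit SD on level leaves the null rate at 4.9%, because it cancels in the change contrast. If childcare shifts change by 0.25, 0.5 or 1 SD of change (1.5, 3 or 6 oz), the rate is 4.9%, 4.2% or 3.2%.

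**5. Strata cut on a screening measure.** If that measure correlates 0.5 with the analysed recall, the planned model's null rate is 4.3–4.7%. The power gain from adjusting remains, since it comes from conditioning on the recall value itself.

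**The case against.** **Neither factor is in the model.** A reader might infer this. For the primary outcome it is too strong: baseline intake is the first repeated response, and the contrast is change from it. Being a response is not the same as being conditioned on, however, and step 3 shows that it does not restore the nominal level. For the secondary outcomes, baseline SSB/juice intake is not in the named terms at all.

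**Childcare must matter by construction.** This inference is tempting because drinks supplied by childcare are left out of the recall. But the Measures section describes the same recall at every assessment. For a child whose care arrangement does not change, the exclusion shifts the level and cancels in change. Nothing in the article shows that childcare predicts change.

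**The stratifying measure is not stated.** This stands. Intake was also assessed at screening for the 12-oz criterion. If that value formed the strata, the null rate is close to nominal and the remaining loss is one of efficiency.

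**The planned power is met.** At 5% the planned model stays above 80% in these scenarios, so the trial is not underpowered on this ground alone. Part of the shortfall at 2.5% belongs to the Bonferroni adjustment: a plain t test with 17 per arm has about 71% power at that level.

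**An article condenses the plan.** A full covariate list may sit in an analysis plan that is not shown, and the text says what the model will include, not that it includes nothing else. But the article does commit to a covariate rule, and that rule tends to exclude the stratification factors. The confounder route remains open to them, though it is unlikely to be taken.

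**Conclusion.** The point holds as a loss of efficiency, with conservatism that depends on how the strata were formed. At nominal 5% the planned contrast runs at about 2.4–3.7% if strata were cut on the analysed recall, and at about 4.3–4.7% if they were cut on a screening measure correlated 0.5 with it. Conditioning on baseline is worth roughly 5 to 10 points of power at 5%, and 6 to 15 at 2.5%, with the larger gain at lower rho. The Discussion section concedes that a single 24-hour recall varies considerably from day to day, which points toward the lower end for rho. Baseline intake accounts for almost all of this; childcare contributes only if it predicts change.

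It would be wrong to infer that the planned test is biased or too liberal. The error runs in the conservative direction. The figures rest on the assumed rho, cut-point, block size and childcare prevalence, on complete data, and on reading 6.0 as the SD of change.

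**What to change.** State in Data analysis that the primary model takes the 3- and 6-month intakes as the responses, with group, visit, group-by-visit, baseline SSB/juice intake (continuous) by visit, and childcare status by visit. Specify both covariates in advance, regardless of the confounder rule. A constrained-baseline model, with the arms sharing one baseline mean and childcare-by-visit added, is an equivalent option.

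Baseline must leave the response vector if it becomes a covariate. Keeping it in both places leaves no residual at the first visit, which a common-variance random-intercept model cannot represent. Simulated that way with 42 analysed, the null rate is 2.7%, 3.4% and 4.4% at rho 0.2, 0.4 and 0.6, against 2.4%, 2.6% and 3.8% in the same runs without the covariate, so the nominal level is mostly not recovered. Covariates should enter by visit; a childcare main effect alone, in a model that keeps baseline as a response, hardly alters the change contrast.

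With complete data, the two-visit model with all covariates by visit gives the same 6-month estimate as the adjusted regression in the working, so those power figures carry over closely. It would also help to state which intake measure and cut-point formed the strata. The cost is wording and a few degrees of freedom; both variables are already collected at baseline.

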### Eligibility criteria

The eligibility criteria were designed to target a population of children with a high risk of obesity, particularly those who have a high consumption of SSBs and juice (SSB/juice) and have mothers who are overweight or obese. The eligibility criteria included maternal BMI of 25–50 kg/m^2^ and a child between the ages of 3–5 who consumed at least 12 oz a day of SSBs/juice (including 100 % fruit juice, fruit drinks, sport drinks, caloric sodas, sweetened teas, and flavored milks). Mothers were required to have a smartphone with an active data and text-messaging plan. Exclusion criteria for mothers included: participation in another weight loss program, pregnancy within the last 6 months, planning to become pregnant in the next 6 months, planning on moving from the study area within the 6-month study period, maternal diagnosis of schizophrenia, bipolar disorder or hospitalization for a psychiatric diagnosis in the past year, or unable to participate in alternatives to sedentary behavior including standing and walking. Children were not eligible if they had a medical condition that would preclude changes in dietary intake or physical activity.

### Recruitment

Participants were recruited from several counties within and surrounding a large metropolitan area in North Carolina, USA. Recruitment methods included flyers, contact with daycares, pediatricians’ office, and WIC clinics, in addition to online advertising on local parents’ websites and Facebook. Interested participants completed an online screening survey to determine their eligibility. Women who met initial eligibility requirements were then followed up by phone call for additional screening. Fully eligible participants attended an in-person orientation session at a university-based research clinic where they provided written informed consent to be in the study to the principal investigator and completed the baseline assessment. Figure 1 depicts the flow of participants from recruitment through the end of the study.

**Fig. 1 Fig1:**
[figure not shown]
Flow of participants

### Sample size and statistical analysis

The primary outcome for the study was change in child SSB/juice intake in fluid ounces from baseline to 6 months. Based on evidence from three previous studies that resulted in significant SSB/juice reductions in children [14, 29, 30], the study was powered to detect a difference of a 6-oz reduction between groups at 6 months, with a within-group standard deviation of 6.0. Therefore, with 80 % power at an alpha level of .05 and accounting for 20 % attrition, the study required 21 participants per group for a minimum of 42 total participants to detect a significant difference in SSB/juice reduction.

### Intervention

The Smart Moms intervention was developed based on Social Cognitive Theory (SCT), which proposes that individual, social and environmental factors interact in a reciprocal manner (i.e. reciprocal determinism) to explain behavior [31]. The Smart Moms intervention included behavior change strategies that specifically targeted the following constructs from SCT that have been associated with sugar-sweetened beverage and juice consumption in previous studies: self-efficacy, outcome expectations, perceived barriers, self-regulation, observational learning, and aspects of the home environment (Table 1). In addition, the intervention targeted positive reinforcement and limit setting within the home, as they are additional strategies that are associated with family behavior change [32]. The overall goal was to use SCT to target the behavior of mothers of young children to, in turn, promote behavior change in the child.

**Table 1 Tab1:** Mapping theoretical constructs to behavioral intervention strategies

Determinant	Strategies
Self-efficacy	Prompt self-monitoring Set short-term goals Provide tailored performance feedback
Outcome Expectations	Provide general information about risk of obesity in young children Provide general information on relationship between SSBs and obesity
Perceived Barriers	Prompt barrier identification Provide strategies to overcome barriers Prompt behavior change with cues to action/encouragement
Self-Regulation	Prompt self-monitoring Set short-term goals
Home Environment	Environmental restructuring
Limit Setting	Provide tailored performance feedback Stress management
Positive Reinforcement	Provide contingent rewards Praise child for behavior
Observational Learning	Provide information on mother as behavioral role model for child

